### Statistical analysis

The statistics and analysis of all data will be conducted by an independent researcher who does not participate in the experiment. We will use the SPSS 22.0 statistical software for data analysis. Descriptive statistics will be used to describe the demographic data of sample groups, while the normality of the distribution of each parameter will be checked by histogram and the Kolmogorov-Smirnov test. A chi-squared test will be used to assess the sample characteristics and gender.

The measurement data were expressed as mean ± standard deviation (SD) or median (interquartile range) [M (IQR)]. The analysis of variance will be used to test the between-group differences for the PSQI, ISI, DBAS, HAMA, HAMD, FS-14 scores, and sleep diary. As to the comparisons of the three groups, normality and homogeneity of variance are analyzed by variance analysis. If the variance is not uniform or normality is not conformed, the Mann-Whitney *U*-test will be used. Counting data is chi-square test. All statistical tests will be conducted bilaterally, and *P* < 0.05 indicates statistical significance. Data analysis will follow the intention-to-treat principle including participants who are randomly assigned. Missing data will be input with the last observation carried forward method.

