## Methods and design

### Study design

This study is a single-center, open label, randomized controlled trial and will be completed in the insomnia clinic of the Acupuncture and Rehabilitation Department of the Affiliated Hospital of Nanjing University of Chinese Medicine from 01 June 2020 to 30 December 2021. This study follows the principles of Consolidated Standards of Reporting Trials (CONSORT), [42] and Standards for Reporting Interventions in Clinical Trials of Acupuncture(STRICTA) [43] will recruit 90 subjects and randomly assign them to the acupuncture group, the TCM-eCBT-I group, and the acupuncture combined with the TCM-eCBT-I group, at a 1: 1: 1 ratio. Subjects will be interviewed before recruitment, by completing a structured insomnia diagnosis process (refer to the 2017 China Sleep Diagnostic [44] - Insomnia Diagnosis Process) to diagnose chronic insomnia, and they will be screened for other sleep disorders, mental disorders, and serious physical diseases and through formal medical history and sleep symptoms. All subjects also need to take PSQI assessment and record one week sleep diary in order to obtain baseline assessment data. Subsequently, 4 weeks of treatment and 24 weeks of follow-up will be conducted.

All subjects will complete the following scale evaluation: PSQI, ISI, and sleep diary to evaluate sleep; DBAS to evaluate sleep cognition and belief; HAMA and HAMD to evaluate mental state; and FS-14 to evaluate mental and physical fatigue. The above scales will be evaluated online in the insomnia TCM system during the 0th week, 4th week, 8th week, 16th week, and 28th week. Subjects will sign an informed consent form after evaluating the conformity for inclusion. The test process is shown in Fig. 1, and the time point of the assessment is shown in Fig. 2.

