### Randomization and allocation concealment

The statistical expert from the Faculty of Medical Statistics and Epidemiology from the Affiliated Hospital of Nanjing University of Chinese Medicine will use the statistical software SPSS (IBM SPSS statistics version 22.0, USA) to generate 3 different random number lists, each of which contains 30 numbers. The random numbers in each list will be sorted in ascending order. The randomization schedule calculated in no. 1–30 is the acupuncture group, no. 31–60 is TCM-eCBT-I group, and no. 61–90 is the acupuncture combined with TCM-eCBT-I group. According to the disclosed method, [45] the allocation sequences are enclosed in sealed envelopes with a unique identification number. The envelope will be sent to an investigator in charge of the group assignments. The investigator will specify in the envelope who and when to open the randomly assigned envelope. The number will appear on all report forms to maintain participant confidentiality. During the study, generation and distribution of random number lists, recruitment of subjects, practice by acupuncturists, assessment, data management, and statistical analysis will be independently conducted by different researchers.

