### Participants

#### Inclusion criteria

The inclusion criteria are as follows:
18–60 years old, no gender limitation (either sex)Meeting the diagnostic criteria for chronic insomnia in ICSD-3 [46]PSQI score > 5 points [47]Not accepted in the past month sedative and hypnotic drugs, acupuncture, and CBT-I treatmentHaving smart terminals (such as smartphones, tablets, computers) and knowing how to use WeChatNo communication and cognitive impairment, voluntarily accept random grouping, and sign the informed consent

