### Outcome measures

#### Primary outcome measures

The PSQI is a questionnaire to assess sleep quality. It consists of six aspects: sleep quality, sleep time, sleep efficiency, sleep disorders, hypnotic drugs, and daytime dysfunction. The total score of PSQI is 0–18 [56]. Sleep quality is negatively correlated with PSQI score. PSQI Chinese version has high reliability and validity and can be used as an effective tool for sleep screening and evaluation in clinical and scientific research [57, 58] PSQI > 5 points indicates that clinical treatment may be required [59] In this study, PSQI > 5 points will be used as the standard for chronic insomnia.

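### The score comparisons are planned as analysis of variance with no baseline adjustment stated, although every scale is measured at week 0; this gives up precision and leaves chance baseline imbalance in the estimate

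*Protocol article*

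**What the plan says.** The PSQI is the only scale under Primary outcome measures in the protocol article: "The PSQI is a questionnaire to assess sleep quality". Statistical analysis then names the between-group test for it and for the other scales: "The analysis of variance will be used to test the between-group differences for the PSQI, ISI, DBAS, HAMA, HAMD, FS-14 scores, and sleep diary". The fallback is also given: "If the variance is not uniform or normality is not conformed, the Mann-Whitney *U*-test will be used". No covariate, analysis of covariance or repeated-measures model is named anywhere in the article.

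The baseline values will exist. Study design states: "All subjects also need to take PSQI assessment and record one week sleep diary in order to obtain baseline assessment data". It also sets the schedule for all scales: "The above scales will be evaluated online in the insomnia TCM system during the 0th week, 4th week, 8th week, 16th week, and 28th week". Inclusion criteria use the same instrument as an entry threshold: "PSQI score > 5 points".

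Randomization and allocation concealment describes using SPSS "to generate 3 different random number lists, each of which contains 30 numbers", one list per arm, and mentions no stratification by baseline severity.

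**The concern.** A patient's score at week 4 or later usually depends on the score at entry. An analysis of variance of follow-up scores leaves that dependence in the error term, where a model with the week-0 value would remove it. With 30 per arm and no stratification described, the arms can also differ at baseline by chance, and part of such a difference is then carried into the estimated treatment effect. Neither the design nor the stated analysis deals with this, although the information needed is collected from every patient. In a trial whose own limitations statement calls the sample too small, the result is wider confidence intervals than the data require, and point estimates that are open to dispute if the baseline table shows a visible difference.

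**Working it through.** **Inputs from the article.** Three arms, 90 patients, so 30 per arm; 72 evaluable after the 20% loss allowance (72 / 0.80 = 90), so 24 per arm; two-sided 5% tests. The article gives no standard deviation and no correlation between baseline and follow-up PSQI, and it has no figure on this point to reproduce.

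**Assumption.** The correlation r is taken as 0.3, 0.5 or 0.7. The change-score formula also assumes the same SD at baseline and follow-up.

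**Step 1: chance imbalance at baseline.** The difference in mean baseline score between two arms of n has SD √(2/n) in units of the baseline SD.
- n = 30: √(2/30) = 0.26; 95% limit 1.96 × 0.258 = 0.51.
- n = 24: √(2/24) = 0.29; 95% limit 0.57.

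At the 95% limit with 30 per arm, r × 0.506 = 0.15, 0.25 and 0.35 SD is carried into the unadjusted follow-up difference at r = 0.3, 0.5 and 0.7.

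**Step 2: variance of the arm contrast, relative to analysing follow-up scores (= 1).** Change scores: 2(1 − r). Covariance analysis: 1 − r². Covariance analysis relative to change scores: (1 − r²) / [2(1 − r)] = (1 + r)/2.

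| | r = 0.3 | r = 0.5 | r = 0.7 |
|---|---|---|---|
| Change v follow-up scores, 2(1 − r) | 1.40 | 1.00 | 0.60 |
| Covariance analysis v follow-up scores, 1 − r² | 0.91 | 0.75 | 0.51 |
| 30 per arm is worth 30/(1 − r²) | 33 | 40 | 59 |
| 24 per arm is worth 24/(1 − r²) | 26 | 32 | 47 |
| Covariance analysis v change scores, (1 + r)/2 | 0.65 | 0.75 | 0.85 |
| 30 per arm is worth 30 / [(1 + r)/2] | 46 | 40 | 35 |

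**Step 3: what this means for a pairwise comparison of follow-up scores.** At 30 per arm, the difference detectable with 80% power is (1.960 + 0.842) × 0.258 = 0.72 SD unadjusted. Multiplied by √(1 − r²), it becomes 0.69, 0.63 and 0.52 SD. A true difference with 80% power unadjusted would have about 84%, 90% and 97.5% power adjusted.

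**Step 4: the unadjusted test, given the imbalance that occurred.** If the baseline difference is k standard errors, the null test statistic has mean rk and SD √(1 − r²).
- k = 1: conditional two-sided error 5.0%, 4.8% and 3.9% at r = 0.3, 0.5 and 0.7.
- k = 1.96: 7.9%, 12.9% and 20.5%.

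An ordinary imbalance does not inflate the error rate; an unusual one does. Averaged over all randomisations the rate is 5%.

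**The case against.** Four points can be made for the plan.

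*The planned test is valid.* This stands. A reader might infer from the baseline argument that the unadjusted comparison is biased or breaks its 5% level. It does not: it is unbiased over randomisations, and its standard error already allows for chance imbalance. The conditional error rates above 5% arise only at the edge of what chance produces.

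*The article does not say what is analysed.* This stands in part. The statistical section speaks of scores without saying follow-up value or change, and names no primary time point. Sample size uses a PSQI reduction rate with responder proportions of 75%, 65% and 45%. The documents therefore do not settle that the primary comparison is an analysis of variance of follow-up scores. If change is analysed, the gain differs but remains for any r below 1. If a responder rate is compared, none of the figures above apply. It would likewise be wrong to infer that baseline adjustment of the scores repairs the power for those proportions.

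*Model terms may be in a fuller document.* This is possible. But the article names the test and its fallback, and an analysis that followed that wording would be unadjusted.

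*The gain may be small.* At r = 0.3 it is worth three patients per arm against follow-up scores, and the entry threshold on the PSQI may lower r. Nor is baseline adjustment the only way to gain precision without more patients: the four post-baseline visits, modelled together, are another.

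**Conclusion.** The point holds as one of efficiency and of conditional imbalance, not of validity. The stated method sets aside a baseline value that every patient provides. Against an analysis of follow-up scores, the loss equals about 3, 10 or 29 patients per arm at r = 0.3, 0.5 or 0.7 (33, 40 and 59 less 30). Against change scores it equals about 16, 10 or 5 (46, 40 and 35 less 30). The range rests on assumed correlations and, for change scores, on equal SDs at baseline and follow-up. The direction does not: covariance analysis is more precise than follow-up scores for any r other than zero and than change scores for any r below 1, apart from one degree of freedom. The change should be made, but leaving it out would not invalidate the trial.

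**What to change.** State in Statistical analysis that each scale is compared by analysis of covariance, with arm and the week-0 value of that scale as terms. Alternatively, specify a mixed model over weeks 4, 8, 16 and 28 with the week-0 value as covariate. State that the dependent variable is the follow-up score. Report adjusted mean differences with 95% confidence intervals for the combined arm against each single therapy, the two contrasts in the hypothesis at the end of Background.

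The rule on normality, equal variance and the Mann-Whitney test must be reworded to fit, for example by checking the model residuals. If the mixed model is chosen, the last-observation-carried-forward sentence needs to be reconciled with it.

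The cost is one residual degree of freedom in the covariance analysis (90 − 3 = 87 becomes 86) and a short analysis amendment. No new data are needed. Recruitment has begun and the article requires ethics approval for revisions, so the amendment should be made and dated before any results are seen, so that the adjustment cannot be taken for a post hoc choice.

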**Methods and analysis:**

This study is a single-center, open-label, randomized controlled trial. Ninety subjects will be recruited and randomly assigned to three groups: the acupuncture group, the TCM-eCBT-I group, and the acupuncture combined with TCM-eCBT-I group, in a ratio of 1:1:1. We will evaluate the Pittsburgh Sleep Quality Index (PSQI) and Dysfunctional Beliefs and Attitudes About Sleep Scale (DBAS), Insomnia Severity Index (ISI), sleep diary, Hamilton Anxiety Scale (HAMA), Hamilton Depression Scale (HAMD), and Fatigue Scale-14 Scale (FS-14) scales. All adverse reactions will be assessed through the ADVERSE event table. All outcomes will be evaluated online at 0 weeks, 4 weeks, 8 weeks, 16 weeks, and 28weeks.

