In the early stage, we developed the insomnia TCM system for chronic insomnia based on WeChat public platform (software copyright, registration number: 2019SR0900086), which is used for TCM diagnosis, information collection, and management of chronic insomnia. It includes modules such as sleep self-test, personal files, tracking, and health education. Baduanjin exercise is a popular traditional Chinese fitness method that combines physical movement, breathing, and psychological adjustment. By stimulating the meridians and organs, [37, 38] it can improve sleep. Five-element music guided by the basic theory of traditional Chinese medicine has a unique curative effect in treating insomnia [39]. We can make a comprehensive analysis according to the syndrome differentiation of patients and choose the corresponding treatment strategy [40, 41].

In order to take advantage of the unique advantages of traditional Chinese medicine in treating insomnia and to explore suitable eCBT-I for Chinese people, this study realizes eCBT-I based on the health education module of the insomnia TCM system, incorporating the Baduanjin exercise and the five-element music, to form TCM-eCBT-I. This study aims to construct a convenient and feasible TCM-eCBT-I, to combine the advantages of acupuncture and TCM-eCBT-I, and to explore the chronic disease management model of acupuncture in the treatment of chronic insomnia. Meanwhile, the short-term and long-term efficacy of acupuncture, TCM-eCBT-I, and acupuncture combined with TCM-eCBT-I will be evaluated to provide information for clinical decision-making. Our hypothesis is that acupuncture combined with TCM-eCBT-I is more effective than TCM-eCBT-I or acupuncture single therapy.

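### The hypothesis is that the combination beats each single therapy, but the planned test of PSQI is a three-group ANOVA with no named contrast or visit, so a significant result need not support it

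*Protocol article*

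**What the plan says.** The Background section of the protocol article gives the hypothesis: "Our hypothesis is that acupuncture combined with TCM-eCBT-I is more effective than TCM-eCBT-I or acupuncture single therapy". The natural reading is two directed comparisons, combined versus acupuncture and combined versus TCM-eCBT-I.

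Under Statistical analysis, "The analysis of variance will be used to test the between-group differences for the PSQI, ISI, DBAS, HAMA, HAMD, FS-14 scores, and sleep diary". If the assumptions fail ("If the variance is not uniform or normality is not conformed"), the Mann-Whitney U-test takes over, without saying which pairs are compared or at what level. "All statistical tests will be conducted bilaterally", and P "< 0.05 indicates statistical significance". No contrast and no order of testing is given.

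The Primary outcome measures section describes the PSQI ("The PSQI is a questionnaire to assess sleep quality") and attaches no time point to it. Study design has the scales completed "during the 0th week, 4th week, 8th week, 16th week, and 28th week", and the Abstract agrees: "All outcomes will be evaluated online at 0 weeks, 4 weeks, 8 weeks, 16 weeks, and 28weeks". That is one baseline and four post-baseline assessments. The Sample size section uses expected rates of 75% (combined), 65% (acupuncture) and 45% (TCM-eCBT-I), and it too names no pairwise comparison.

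**The concern.** A three-group ANOVA asks whether the three means are all equal. It rejects for any departure from equality, including two in which the hypothesis is false: only the single therapies differ, or the combination equals acupuncture and TCM-eCBT-I lags behind both. The planning rates lean towards the second pattern. The combination is expected to exceed TCM-eCBT-I by 30 percentage points but acupuncture by only 10, so TCM-eCBT-I being low would drive most of the signal.

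What is at stake is the headline claim that adding TCM-eCBT-I to acupuncture helps. A significant PSQI result under the stated test could be read as support for that claim when the data show nothing of the kind. The unnamed visit adds to this. End of treatment (week 4) and end of follow-up (week 28) answer different questions, and the text leaves open which one carries the primary result. The trial is open-label and subjects complete the online scale assessments themselves, so fixing contrast and visit in advance matters more than usual.

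**Working it through.** **Inputs from the protocol article.** 30 per arm randomised, 24 per arm evaluable (72 of 90); rates 75/65/45%; two-sided 0.05; four post-baseline visits. **Assumed, because not given:** the PSQI effect in SD units and the correlation between visits.

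**The plan's own figure.** 72/0.8 = 90 reproduces the dropout step. The 72 does not reproduce as a three-group chi-square at 0.05. The mean rate is 0.617 and w² = [Σ(p − 0.617)²/3]/(0.617 × 0.383) = 0.0658. The noncentrality is therefore 72 × 0.0658 = 4.74, giving 48% power (90 subjects: 5.92, 58%). That shortfall is a separate matter. It appears here only to show that the simulation in step 2 agrees with the formula.

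**1. How specific is the ANOVA?** Take standardised benefits of (0, 0, −d) for combined, acupuncture and TCM-eCBT-I, so the hypothesis is false. Noncentrality λ = n × (2/3) × d²; at n = 30, λ = 20d². Reject when F(2, 87) > 3.10.

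| d (SD) | λ at 30 per arm | P(reject), 30 per arm | P(reject), 24 per arm |
|---|---|---|---|
| 0.5 | 5.0 | 49% | 40% |
| 0.65 | 8.45 | 73% | 62% |
| 0.7 | 9.8 | 79% | 69% |
| 0.8 | 12.8 | 89% | 81% |

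In every row the combination adds nothing to acupuncture.

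**2. The protocol's own rates, with no SD needed.** Binomial simulation at 75/65/45%, using the three-group chi-square and pooled two-sample z tests at two-sided 0.05. This uses responder rates as in the Sample size section, not PSQI means.

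| | 30 per arm | 24 per arm |
|---|---|---|
| Three-group test significant | 59% | 49% |
| Combined significantly better than acupuncture | 13% | 11–12% |
| Combined significantly better than TCM-eCBT-I | 67% | 59–60% |
| Combined significantly better than both | 12% | 10% |

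Among significant three-group results, about 80% do not show the combination beating both arms.

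**3. Several visits, if each has its own ANOVA.** With no effect anywhere and four independent visits, 1 − 0.95⁴ = 18.5%. Simulating 3 × 30 subjects with exchangeable visit correlation, the chance of at least one P < 0.05 for PSQI is about 17% at correlation 0.4, 15% at 0.6 and 11 to 12% at 0.8.

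**4. After the fix.** Both contrasts are required at one visit, each at two-sided 0.05 and favouring the combination. When the combination equals acupuncture, false support falls to about 2 to 2.5%. Power at the planning rates is the 12% (10% at 24 per arm) in step 2. The limiting contrast is 75% versus 65%, which alone would need 329 per arm for 80% power and 440 for 90%.

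**The case against.** The strongest reply has four parts.

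First, the text nowhere says that the ANOVA is repeated at each visit. That is correct. It is an inference from the lack of a named visit or longitudinal model, so the 11 to 17% figure is conditional on it. The main point is not: one ANOVA at one visit, or the group effect in a repeated-measures ANOVA, is just as unspecific.

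Second, post-hoc contrasts and multiplicity rules are often left to an analysis plan, and the Mann-Whitney fallback, being a two-sample test, suggests that pairwise comparisons are intended. This has weight, and the absence of a post-hoc procedure alone would not be a finding. But the article does fix a test and a threshold, and they do not match its own hypothesis.

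Third, the article also aims to evaluate all three treatments for clinical decision-making, and an omnibus test suits that aim. It does, which is a reason to keep the ANOVA as secondary. It does not make it a test of the stated hypothesis.

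Fourth, the effect sizes are assumed. The upper end, 79 to 89%, needs 0.7 to 0.8 SD and should not be quoted alone. If acupuncture and the combination were both at 65% against 45%, the gap would be nearer 0.5 SD and the rejection rate nearer 49%.

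A reader might also infer that unadjusted pairwise tests across the visits will inflate the error further still. The plan states no such tests. With three groups, pairwise tests done only after a significant ANOVA keep the familywise error at 5% at each visit, so no such rate can be charged to this plan.

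**Conclusion.** The point holds. Followed as written, the analysis can give a significant PSQI result that says nothing about whether the combination beats each single therapy. The size is about 49 to 89% rejection when the combination only equals acupuncture (assumed 0.5 to 0.8 SD deficit for TCM-eCBT-I, 30 per arm). At the planning rates it is about 59% significant against about 12% that show the hypothesis. The second pair rests on the protocol's own responder rates and not on an assumed SD.

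Two stronger readings are not supported. The document does not say that any significant visit counts as success, so an error rate above 5% follows only if separate ANOVAs are run by visit. Nor does it state a rule by which an omnibus result is declared proof of the hypothesis; the fault is that nothing in the stated test separates the two.

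**What to change.** In Primary outcome measures and Statistical analysis, define the primary analysis as two PSQI contrasts, combined versus acupuncture and combined versus TCM-eCBT-I, at one visit named before analysis. State whether the contrast is in PSQI score or in the reduction rate used for the sample size. The visit is the sponsor's choice: week 28 fits the long-term aim and week 4 the short-term one.

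Claim the hypothesis only if both contrasts favour the combination and both are significant at two-sided 0.05. Because both are required, no alpha split is needed. Keep the three-group ANOVA, acupuncture versus TCM-eCBT-I, the other visits and the other scales as secondary.

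The edit is wording only, and the article describes recruitment as still open. The real cost is power: about 12% to win both contrasts at the planning rates with 30 per arm, and 10% with 24. This should be disclosed. The report should give both contrasts with confidence intervals and should not read a non-significant one as no benefit. The low power is not a reason to keep the ANOVA as primary, since the ANOVA only hides how little the trial can say about its own hypothesis.

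### The fallback for the three-group comparison is a two-sample test (Mann-Whitney), which implies uncorrected pairwise testing and is not the right remedy for unequal variances

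*Protocol article*

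**What the plan says.** All of the following is in the protocol article.

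- **Design (Study design).** Subjects are allocated to three arms: "randomly assign them to the acupuncture group, the TCM-eCBT-I group, and the acupuncture combined with the TCM-eCBT-I group, at a 1: 1: 1 ratio". The scales are completed "during the 0th week, 4th week, 8th week, 16th week, and 28th week", so four of the five assessments fall after baseline.
- **Main test (Statistical analysis).** "The analysis of variance will be used to test the between-group differences for the PSQI, ISI, DBAS, HAMA, HAMD, FS-14 scores, and sleep diary".
- **Assumption checks (Statistical analysis).** The distribution of each parameter "will be checked by histogram and the Kolmogorov-Smirnov test". The text then turns to the three-group comparison: "As to the comparisons of the three groups, normality and homogeneity of variance are analyzed by variance analysis".
- **Fallback (Statistical analysis).** "If the variance is not uniform or normality is not conformed, the Mann-Whitney" U-test is used instead. Either failure, unequal variance or non-normality, leads to the same test.
- **Level (Statistical analysis).** "All statistical tests will be conducted bilaterally, and" P < 0.05 counts as significant. No adjustment for multiple comparisons is mentioned.
- **Hypothesis (Background).** "Our hypothesis is that acupuncture combined with TCM-eCBT-I is more effective than TCM-eCBT-I or acupuncture single therapy". This names two contrasts: the combination against each single therapy.

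**The concern.** The fallback is attached expressly to the comparison of three groups, but the test it names takes two samples. An analyst who reaches this branch must either run the test pair by pair or choose another method after seeing the data. Pair-by-pair testing at a flat 0.05 replaces one test of the three-arm null by up to three tests, each with its own chance of a false positive. PSQI is the primary outcome, so this affects the comparison the trial exists to make.

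The same test is prescribed when variances differ. A rank-sum test compares whole distributions. When spreads differ it is no longer a clean test of a difference in means, which is what the analysis of variance was there to assess.

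The switch depends on checks made on the trial data, so the method, and with it the hypothesis tested, can change from one scale or visit to the next.

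**Working it through.** **Inputs from the protocol article.** Three arms, 1:1:1. Planned size 30 per arm, or 24 per arm before the 20% allowance for loss (72/3 = 24; 72/0.8 = 90; 90/3 = 30). Two-sided level 0.05 for each test. The article gives no standard deviation or distribution for PSQI, so those below are assumptions. The plan states no familywise error that could be reproduced.

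**Step 1: number of tests.** Three arms give 3 × 2 / 2 = 3 pairs per outcome and visit. The hypothesis names 2 of them.

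**Step 2: bounds and large-sample values for all three pairs.**
- Bonferroni bound: 3 × 0.05 = 0.15.
- If the tests were independent: 1 − 0.95³ = 0.143.
- The pairs share arms, so the true value is lower. In large samples with equal arms, at least one pair is significant when the range of three standard normal means exceeds 1.96 × √2 = 2.77. That probability is 0.122.
- For two contrasts sharing one arm, the test statistics correlate at 0.5. The chance that at least one exceeds 1.96 in absolute value is 0.091.

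**Step 3: simulation at the trial's sizes.** No treatment effect, scores rounded to whole numbers, mean 10 and SD 3 assumed, 20,000 runs.

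| Procedure, one outcome at one visit | 24 per arm | 30 per arm |
|---|---|---|
| Any of three Mann-Whitney tests at 0.05 | 0.116 | 0.119 |
| Either of two hypothesised contrasts at 0.05 | 0.086 | 0.089 |
| Kruskal-Wallis | 0.048 | 0.049 |
| Pairs tested only after a significant Kruskal-Wallis | 0.048 | 0.049 |
| Three pairs at 0.05/3 | 0.041 | 0.041 |

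Other runs with slightly different assumptions gave 0.115–0.118 for three pairs and 0.083–0.085 for two. Hence about 0.11–0.12 and 0.08–0.09. The analysis of variance itself stays at about 0.05.

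**Step 4: unequal variances.** Two groups with equal centres, 20,000 runs, rejection rate at 0.05.

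| Setting | Mann-Whitney | Welch t-test |
|---|---|---|
| Normal, SD 1:3, 30 vs 30 | 0.064 | 0.049 |
| Normal, SD 1:3, 24 vs 24 | 0.069 | 0.053 |
| Normal, SD 1:3, 30 vs 20 (larger SD in smaller arm) | 0.084 | 0.048 |
| Skewed (exponential), equal means, SD 1:2, 30 vs 30 | 0.26 | 0.057 |

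For three normal groups of 30 with equal means and SDs 1:2:3: any of three Mann-Whitney tests 0.134, Kruskal-Wallis 0.060, ordinary ANOVA 0.062, Welch ANOVA 0.049.

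**Step 5: separating the effect of repeated visits.** Chance of at least one significant result over four post-baseline visits (30 per arm, between-visit correlation assumed):

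| Correlation | ANOVA at each visit | Three Mann-Whitney tests at each visit |
|---|---|---|
| 0.3 | about 0.17–0.18 | 0.38 |
| 0.8 | about 0.12 | 0.26 |

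Much of the four-visit total is therefore present without the fallback.

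**The case against.** **The article is condensed, and a post-hoc correction may stand in an analysis plan that is not shown.** This is true of the correction. The article does not list three pairwise tests or declare them uncorrected; that is what a two-sample test on three groups at a flat 0.05 implies. But the wrong test is named outright, so that part is not an omission.

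**The doubling depends on counting all three pairs.** This stands. For the two hypothesised contrasts the error is 0.08–0.09, less than double. If the combination had to beat both single therapies, the chance that both contrasts are significant under no effect is about 0.01, with no inflation. The word linking the two single therapies in the hypothesis leaves this open.

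**The variance problem is easily overstated.** This also stands in part. If treatment does nothing at all, the randomised arms have identical distributions and Mann-Whitney keeps its level. Allocation is equal, and carrying the last observation forward tends to keep the analysed arms equal. With symmetric data the excess is then small. The 26% figure applies when equality of means is the question and shapes differ. Kruskal-Wallis shares the weakness (0.060 above).

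**A reader might infer that the fallback drives the error over four visits to between a quarter and two fifths.** The documents do not support charging that to the fallback. Step 5 shows that repeated visits alone take plain ANOVA to about 12–18%. That is a separate multiplicity question.

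**The branch may seldom be used.** This cannot be settled. In one run with PSQI-like whole-number scores, normality failed in at least one arm in 52% of simulated trials with the Lilliefors form of the Kolmogorov-Smirnov test, but in under 1% with the uncorrected form. The article does not say which is meant.

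**Conclusion.** The point holds in a limited form. The protocol article names a two-sample test for a three-group comparison, and the sentence needs replacing whatever the size of the effect. When the branch is used as written, the implied familywise error per outcome and visit is about 0.11–0.12 for all three pairs, or about 0.08–0.09 for the two hypothesised contrasts, against 0.05. These figures assume no treatment effect, 24 to 30 per arm, and pairwise tests without correction. They depend little on the assumed SD.

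Mann-Whitney is also not the right remedy for unequal variances if means are to be compared. The cost is modest with equal arms and symmetric data (about 0.06–0.07 at an SD ratio of 1:3) and larger with skewed data or unequal arms.

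A reader might go further and conclude that analysis of variance must be abandoned for all scales. Nothing in the document requires that; the error lies in the fallback. Letting a normality pre-test choose the method visit by visit is a secondary weakness.

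**What to change.** Replace the fallback sentence in Statistical analysis with text along these lines:

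- **Unequal variances:** Welch ANOVA with Games-Howell pairwise contrasts.
- **Non-normality:** Kruskal-Wallis, followed by pairwise rank tests only if it is significant, or Dunn tests with Holm correction. With three groups the gated version is a closed procedure. If all three arms are equal, the first test holds 5%. If only one pair is equal, only one true null remains to be rejected, also at 5%.
- **Preferably, for PSQI:** fix one method in advance, for example Welch ANOVA with Kruskal-Wallis as sensitivity analysis. A Kolmogorov-Smirnov result then does not choose the test at each visit, and no rule is needed for the case where both assumptions fail.

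Multiplicity across the four post-baseline visits should be handled separately, because this change does not address it.

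The cost is a sentence or two of wording, with no new data or patients. The downside is slightly fewer nominally significant pairwise results.
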